### Multiple sclerosis quality of life-54 (MSQOL-54)

6.2.

The MSQOL-54 is a multidimensional health-related quality of life measure. It consists of the Short Form 36 (SF-36) (43) along with 18 additional items pertinent to people with MS. The 36 items grouped into 8 domains: physical function, social function, physical role limitations, emotional role limitations, pain, energy/fatigue, mental health, and general health.

## Statistical analysis

7.

A two-way repeated measures ANOVA will be undertaken to analyse the data. For the primary analysis, the effects of the main factors “Group (4 groups)” and “Time (7 time points)” and the interaction of “Group * Time” will be assessed on HPT scores. Prior to analysis, tests for normality will be undertaken and, if the assumption of normality is violated, a Wilcoxon rank-sum test will be used. For the secondary analyses, similar analyses will be performed for outcomes (HPT scores, quality of life, CE, SICI, LICI and ICF) at pre intervention, post 5-days intervention, W2, W4, W6, W8 and W12.

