**Figure 1 F1:**
[figure not shown]
Flow diagram of randomization, intervention and assessments. This figure shows the randomization of the participants into 4 groups and the allocated intervention and assessment sessions throughout the trial. MS: Multiple Sclerosis; tDCS: Transcranial direct current stimulation.

**Group 1: Control group** (*n* = 18): Patients in this group will participate in hand training sessions only based on the current standard in clinics for 8 weeks. During week 1 this will be provided in 5 sessions over 5 consecutive days (30 min with rest) and during weeks 2–8, participants will have 2 sessions per week. They will have the following assessments: baseline assessments (before training); assessments during hand training (week 1, at the end of 5 consecutive training sessions and end of week 2, 4, 6 and 8); and follow-up assessments (week 12).

**Group 2: Experimental group (Hand training only**) (*n* = 18): Patients in this group will participate in hand training sessions in the exact time frame as Group 1 but they will practice a new motor skill (Figure 2) during their hand training sessions. The time frame for the assessments will be exactly the same as for Group 1.

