### Rationale for the sample size

4.4.

The study is a within-subject, repeated measures study with one between factor (Group) with four levels and one within factor (Time) with seven time points. As we are predicting an effect size of 0.30 (medium to high), 16 subjects per group (a total of 64 subjects) is needed to achieve 80% power with a 5% significance level. Allowing for a 10% drop out rate, each group will need 18 subjects.

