**Figure 3 F3:**
[figure not shown]
Timeline for intervention and assessments for one participant. This figure shows the timeline for the allocated intervention and assessment sessions for a participant in this study. Baseline assessment will be completed for each participant and then they start the hand training sessions ± tDCS intervention (5 sessions during week 1). During weeks 2−8, participants will have 2 hand training sessions per week. Then at the end of weeks 1, 2, 4, 6, 8 and 12, they will go through some post-intervention assessments or follow-up assessments.

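### Pre-intervention 9-HPT is one of seven outcome levels in the primary repeated-measures ANOVA and is not adjusted for, which costs precision that a baseline-adjusted model would recover

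*Protocol article*

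**What the plan says.** Section 7 (Statistical analysis) of the protocol article fixes the primary method: "A two-way repeated measures ANOVA will be undertaken to analyse the data". The factors are Group with four levels and "Time (7 time points"; both main effects and their interaction "will be assessed on HPT scores". No baseline covariate appears.

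The visit schedule shows what the seven levels are. The Group 1 description in section 4.3 lists "baseline assessments (before training", and the other groups follow the same time frame. The Figure 3 legend places all later assessments "at the end of weeks 1, 2, 4, 6, 8 and 12", which is six visits. Section 7 itself gives the points for the secondary analyses as "at pre intervention, post 5-days intervention, W2, W4, W6, W8 and W12", which is again one pre-intervention point and six later ones.

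Section 4.4 (Rationale for the sample size) uses the same layout, with "one within factor (Time) with seven time points". It asks for 16 patients per group (64 in total) and then adds: "Allowing for a 10% drop out rate, each group will need 18 subjects". The article does not say how a missed visit is handled.

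**The concern.** At the pre-intervention visit no treatment has been given, so randomised groups differ there only by chance. Making that visit an outcome level has two consequences for the Group main effect: one of its seven levels carries no treatment effect, and any chance imbalance at baseline stays in the comparison. The baseline score is planned for every patient and is likely to predict later scores, but it is not used as a covariate to reduce residual variance. With 18 patients per group, that is a material loss of precision in the primary analysis.

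A second issue depends on how the model is fitted. A classical repeated-measures ANOVA needs every cell of a patient's row, so one missed visit out of seven removes the patient. The sample-size allowance is described as dropout only.

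**Working it through.** **The plan's own figures.** The dropout step reproduces: 16/0.9 = 17.8, rounded up to 18; 4 × 18 = 72. The 64 can be neither confirmed nor refuted, because the within-patient correlation, the sphericity correction and the effect being powered are not given. If 0.30 is read as Cohen's f, 64 comes out for the Group effect only at a correlation of about 0.38 to 0.41 (power 0.808 at 0.4). At 0.5 the Group effect would need 76.

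**Dilution.** Seven Time levels minus six post-baseline visits leaves one, the baseline. With zero expected difference there and a constant difference afterwards, the Group main effect estimates 6/7 of that difference. The noncentrality falls by (6/7)² = 0.73.

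**Precision.** Assume unit variance at each visit, a common correlation r between any two visits (compound symmetry) and a constant post-baseline effect. The article gives no correlation, so r = 0.5 and r = 0.8 are shown. Per-patient variances are:

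- A, Group main effect rescaled to undo the dilution: (7/6)² × (1 + 6r)/7
- B, mean of six post-baseline visits minus baseline: (1 + 5r)/6 + 1 − 2r
- C, mean of six post-baseline visits adjusted for baseline: (1 + 5r)/6 − r²

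| | r = 0.5 | r = 0.8 |
|---|---|---|
| A | 0.778 | 1.128 |
| B | 0.583 | 0.233 |
| C | 0.333 | 0.193 |
| A/C | 2.33 | 5.83 |
| B/C | 1.75 | 1.21 |
| A/B | 1.33 | 4.83 |

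**Interaction.** A post-against-baseline contrast within Group × Time behaves like B. The planned test is not that single contrast, however. It is an omnibus test with (4 − 1) × (7 − 1) = 18 numerator degrees of freedom.

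**Power illustration.** Simulation used 1,500 runs, 18 per group, complete data, and one group shifted by 0.693 SD from week 1, which gives f = 0.693 × √3/4 = 0.30.

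| Correlation | Group | Group × Time | Baseline-adjusted mean |
|---|---|---|---|
| 0.5 | 0.65 | 0.47 | 0.96 |
| 0.7 | 0.54 | 0.73 | 0.99 |
| 0.85 | 0.45 | 0.98 | 1.00 |

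**Completeness under a classical fit.** Suppose each post-baseline visit is missed independently with probability q (an assumption), on top of the planned 10% dropout. The expected number of complete patients is 72 × 0.9 × (1 − q)⁶:

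- q = 0: 64.8
- q = 1%: 64.8 × 0.941 = 61.0
- q = 2%: 64.8 × 0.886 = 57.4
- q = 3%: 64.8 × 0.833 = 54.0

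Section 4.4 requires 64.

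**The case against.** **Baseline is not wasted.** A reader might infer that the plan throws the baseline value away. It does not. The Group × Time test uses it, and the hypotheses in section 3.1 are about improvement, so that interaction is arguably the test that matters. The ratios of 2.3 and 5.8 belong to the Group main effect alone. Against a single change-score contrast, the gain from baseline adjustment is smaller: 1.75 at r = 0.5 and 1.21 at r = 0.8. This stands. What remains is that the interaction test is unadjusted and spread over 18 degrees of freedom, and at a correlation of 0.85 even that costs little in the simulation.

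**Nothing in the article discards patients.** A reader might also infer that everyone with one missed visit is excluded by rule. The article states no such rule, and handling of missed visits may sit in an analysis plan that is not shown. The loss follows only from the usual fit of the named method. Its size depends on assumed rates: with 1% missed per visit and no dropout, 1 − 0.99⁶ = 5.9% are lost, which is inside the 10% allowance. With 10% dropout alone, 64.8 patients remain, which meets the 64.

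**There is no bias from the baseline level itself.** Under randomisation, keeping baseline as an outcome level costs precision only. Bias from excluding incomplete patients would need both a complete-case fit and missed visits related to outcome, and the article establishes neither.

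**A constant effect is a simplification.** Hypothesis 3 expects further benefit from training in weeks 2–8, and week 12 falls after training ends. If the effect varies, the 6/7 factor applies to the average of the six post-baseline effects, and that average may not be the quantity of most interest.

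**Conclusion.** The point holds as a badly fixed choice of primary model. The seven-level Time factor can only be read as including baseline, and no adjustment for baseline is named. The cost falls mainly on the Group main effect: 2.3 to 5.8 times the variance of a baseline-adjusted post-baseline mean for correlations of 0.5 to 0.8, under compound symmetry and a constant post-baseline effect. For a change-score contrast the cost is 1.75 to 1.21 times. The correlations are assumed, and a different correlation pattern would move the figures.

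The planned test is inefficient, not invalid. The shortfall in complete patients (about 61 to 54 against 64) is conditional on a classical fit and on 1% to 3% of visits being missed in addition to 10% dropout. The plan should be changed, because the remedy uses data already planned.

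**What to change.** Replace the primary ANOVA with a linear mixed model on the six post-baseline 9-HPT values (weeks 1, 2, 4, 6, 8 and 12):

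- Fixed effects: group, visit, group-by-visit, baseline 9-HPT and baseline-by-visit.
- Covariance: unstructured within patient, with a simpler fallback structure named in advance, and Kenward-Roger degrees of freedom.
- Population: all randomised patients with at least one post-baseline value, in the group to which they were randomised.
- Primary contrast named in advance: for example, the baseline-adjusted group difference averaged over the post-baseline visits, or the difference at one named visit. The gains quoted for the six-visit mean apply only if that average is the contrast chosen.

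Section 4.4 describes the 4 × 7 layout and should be aligned with the new model, stating the effect being powered and the correlation assumed.

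The cost is wording in sections 4.4 and 7; no new data are needed. The statistical downside is more covariance parameters: an unstructured matrix for six visits has 6 × 7/2 = 21 to be estimated from 72 patients, which is why the fallback must be named.

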### Experimental design

4.3.

Enrolled patients will be randomly allocated to one of four groups (*n* = 18 per group). Randomisation will be controlled by one of the investigators using a secure web-based computer-generated sequence which is a commonly used and reliable method for ensuring that study participants are assigned to different groups in a fair and unbiased manner (Figure 1).

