### Manual dexterity: 9 hole peg test (9-HPT)

5.1.

The 9-HPT is considered as a gold standard measure of manual dexterity and most frequently used in MS research and clinical practice (37). During this test patients will sit behind a desk and will be instructed to pick up one peg at the time from the container and place it in a hole as fast as they can, then take them off and put them back to the container again. Their completion time will be recorded for both hands in two consecutive trials.

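### The fallback for non-normal data, a Wilcoxon rank-sum test, cannot test any of the three effects that define the primary analysis of the 4-group by 7-visit design

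*Protocol article*

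**What the plan says.** Section 7 (Statistical analysis) opens with the main method: "A two-way repeated measures ANOVA will be undertaken to analyse the data". For the primary analysis it lists the main effects of Group (4 groups) and Time (7 time points), and adds that "the interaction of “Group * Time” will be assessed on HPT scores".

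The switch to another method follows directly: "Prior to analysis, tests for normality will be undertaken", and "if the assumption of normality is violated, a Wilcoxon rank-sum test will be used". The article does not say which two groups, which visit, or whether raw scores or changes from baseline would be compared.

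The section then extends the approach: "For the secondary analyses, similar analyses will be performed for outcomes". The list that follows includes quality of life and the neurophysiological measures, at the same seven time points.

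Section 4.4 (Rationale for the sample size) rests on the same structure: "one between factor (Group) with four levels and one within factor (Time) with seven time points". Section 4.3 confirms the allocation: "Enrolled patients will be randomly allocated to one of four groups". Section 5.1 describes the primary measure: "Their completion time will be recorded for both hands in two consecutive trials".

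**The concern.** The fallback does not fit the design that it is meant to rescue. A rank-sum test takes two independent samples. It has no place for a third or fourth group, no within-patient factor and no interaction term. If the normality check fails, the effects that Section 7 calls primary have no test.

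Someone following the sentence would have to choose a pair of groups, a visit and a score, or run many pairwise tests. The first leaves the primary result open to choices made after the data are seen. The second inflates the chance of a false positive unless an adjustment is made. In both cases the sample size in Section 4.4, which was set for the 4 by 7 model, no longer describes the analysis performed. Because the secondary outcomes get similar analyses, the same problem may reach them.

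**Working it through.** **Step 1. Set the stated effects against the stated fallback.** The three effects come from Section 7.

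| Stated effect | Degrees of freedom | Can a rank-sum test assess it? |
|---|---|---|
| Group, 4 levels | 4 − 1 = 3 | No. It takes two groups only |
| Time, 7 levels | 7 − 1 = 6 | No. Visits of the same patient are not independent samples |
| Group by Time | 3 × 6 = 18 | No. The test has no interaction term |

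No other section of the article gives a method for more than two groups or for repeated measures when normality fails.

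**Step 2. What the fallback could still do.** The hypotheses in Section 3.1 reduce to contrasts between two groups: new skill against current training (group 2 v 1), active stimulation against skill alone (3 v 2), and active against sham stimulation (3 v 4). A rank-sum test on change from baseline at one named visit would be a valid test of each contrast at that visit. It would use the within-patient pairing through the change score. It would not describe the course over visits, and the article names no such use.

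**Step 3. Count the tests if all pairs were compared.** The article does not plan this. It is a reference case for the size of the problem.
- Group pairs: 4 × 3 / 2 = 6.
- Post-baseline visits: 7 − 1 = 6 (weeks 1, 2, 4, 6, 8 and 12). The six baseline comparisons are left out because they test no treatment effect.
- Tests: 6 × 6 = 36.

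**Step 4. Family-wise error if the tests were independent**, each at 5%: 1 − 0.95^k.
- 6 pairs at one visit: 1 − 0.95^6 = 0.265.
- 36 tests: 1 − 0.95^36 = 0.842.
- The 3 contrasts of Section 3.1 at one visit: 1 − 0.95^3 = 0.143.
- The 3 contrasts at 6 visits: 1 − 0.95^18 = 0.603.

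Pairs share groups and visits share patients, so the tests are positively correlated. These figures are therefore upper bounds, not expected values.

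**Step 5. Family-wise error by simulation**, with no true group difference. Inputs are 4 groups, 16 evaluable patients per group (Section 4.4), raw scores and unadjusted rank-sum tests at 5%. The within-patient correlation is assumed to lie between 0.5 and 0.9, because the article states none.
- 6 pairs at one visit: about 17–22%.
- 6 pairs at 6 post-baseline visits: about 37–63%. The upper end belongs to a correlation of 0.5 and the lower end to 0.9.

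Skewness does not affect these results, because the rank-sum test is unchanged by any monotone transformation of the scores.

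**The case against.** The ANOVA remains the main path, and the fallback operates only if normality is rejected. Nothing in the article shows that it will be: Section 5.1 gives no mean, SD or shape for completion times. This stands, so right skew is used here only as an assumption.

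A reader might infer that the fallback leaves the trial's whole question untested. The article does not support that. The Section 3.1 hypotheses are mostly two-group comparisons, and rank-sum tests on change scores could answer part of them. What is lost is every effect named in Section 7.

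A reader might also count 6 pairs × 7 visits = 42 tests and quote 1 − 0.95^42 = 88% as the false-positive risk. That overstates it. No such set of tests is planned, the count includes baseline, and the formula assumes independence.

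Multiplicity rules are commonly left to a statistical analysis plan, which is not shown, so their absence is not a defect in itself. The error rates above show only what an unadjusted use of the fallback would cost. The switch is also stated in advance and is not an improvised choice, so the objection to pre-testing alone would be minor.

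One might suppose that the signed-rank test, or a multi-group rank test, was intended. The article names the two-sample test, and the signed-rank test would not give a 4-group or interaction test either. The mismatch is therefore a wrong stated rule and not an omitted detail.

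**Conclusion.** The point holds and the sentence is wrong as written. If the normality check fails, the named test can assess none of the three stated primary effects. The pairwise hypotheses would be only partly covered, by a procedure that is not specified.

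That conclusion follows from what the test is and needs no numerical assumption. Its practical weight depends on the check failing, which is plausible for a completion time if it is right-skewed. If unadjusted pairwise tests filled the gap, the nominal 5% would become roughly 17–22% at a single visit and 37–63% over six post-baseline visits, with 84% as the independence upper bound for those 36 tests. The simulated ranges assume 16 patients per group, a within-patient correlation of 0.5–0.9 and comparison of raw scores. The rule should be corrected before any outcome data are examined, because a replacement chosen afterwards would be data-dependent.

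**What to change.** In Section 7, or in the analysis plan if it repeats the rule:

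1. Delete the normality pre-test as a switch, and delete the rank-sum fallback.
2. Fix the 9-HPT analysis scale in advance, for example log completion time.
3. Keep the same Group by Time longitudinal model whatever the distribution, and name the contrasts that answer Section 3.1: group 2 v 1, 3 v 2 and 3 v 4.
4. As a sensitivity analysis, test the same effects with a permutation test or a rank-based longitudinal method.
5. Apply the same rule to the secondary outcomes that receive similar analyses, with each outcome's scale set in advance.

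The cost is a few sentences, with no extra patients, visits or measurements. The downside is that on the log scale 9-HPT effects are reported as ratios of completion time and not in raw seconds. Back-transformed group means can be shown alongside for clinical readers.

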## Outcome

8.

If learning and practicing a new motor skill shows more significant improvement in hand functions in patients with MS compared to practicing the pre-injury well learned upper limb and hand function tasks, this approach can be assessed through a clinical trial first and then be easily adopted by all clinicians as a new approach in restoring the hand functions in this population. Furthermore, if application of within-session repeated a-tDCS is shown to have cumulative significant effects in improving hand functions in people with MS, tDCS may provide a low-risk, non-invasive option as an adjunct interventions during rehabilitation for these patients.

## Discussion

9.

To reduce the impact of this disease on patients, their families, carers, and the aged care sector, we need to assist them in remaining independent for as long as possible (44). In this study we propose a number of initiatives for to have better outcomes for these patients.

We propose several initiatives in this study to improve treatment outcomes for these patients:
1.Choosing upper limb (hand functions) as the target of treatment2.Considering a new training concept for treating manual dexterity3.Using within session repeated application of tDCS4.Using multiple session concurrent application of tDCS and trainingThe following sections will discuss each of these initiatives:

### Upper limb as the target of treatment

9.1.

Upper limb functions and specifically hand functions play an essential role in providing independence for these patients. It has been shown that manual dexterity is usually impaired in these population interfering with daily and social activities and are associated with loss of employment, decreased quality of life and increased health care costs (8, 45). It has been reported and suggested that “MS continues to represent a serious burden for people with MS and the community in terms of both economic impact and QoL. Interventions that slow or prevent the accumulation of disability in MS are likely to have a substantial impact on the economic costs and QoL of people with MS” (46).

In a systematic review, Lamers et al. (2016) reported that rehabilitation research targeting the upper limb functions in MS is rare compared to research targeting the lower limbs (6). A large number of different rehabilitation strategies have been applied to improve upper limb function in this population, ranging from resistance and endurance training on the body functions and structures level to task-oriented training on the activity level (6). It is impossible to determine the effectiveness of a specific rehabilitation strategy for upper limb function due to the diversity of strategies and included patients (EDSS: 1–8) in different studies.

### Considering a new training concept for treating manual dexterity

9.2.

We are proposing that patients should practice a completely new motor skill with their hand fingers rather than practicing pre-injury well-learned tasks repeatedly to trigger the production of oligodendrocytes in M1 area in their brain which will in turn trigger the production of myelin. This learning process and task-dependent neuroplasticity in M1 area will be facilitated by a new developed a-tDCS technique which provides accumulative long-term effect to maximize the effect of hand training sessions in restoring hand functions in patients with MS. (Figure 4).

